### Blinding

This is a single-blind study. Visits will be carried out by an investigator with adequate training in questionnaire administration. This investigator will not participate in the intervention or the evaluation of the results. The intervention will be performed by two researchers (a pain physician and a psychologist). These researchers will not participate in the questionnaire and baseline data collection nor in the data analysis. Researchers who analyze the results will not participate in the questionnaire and baseline data collection or program intervention.

#### General procedures

The study subjects will be assigned to one of two arms, and the intervention program will be compared to the standard-of-care clinical practice. The baseline visit will take place 4 to 6 weeks after hospital discharge, and two follow-up visits will take place 3 and 6 months after.

The intervention program will consist of an early care therapeutic education on prevention and management of PICS and chronic pain during the three scheduled medical visits within the first 6 months after hospital discharge and psychological treatment for patients at risk of emotional distress.

### Recruitment and participant timeline

Patients who are eligible for the study will be contacted approximately 1 month after discharge from the hospital, they will be informed about the study, and they will be asked to participate. Those who accept to participate will have to complete a baseline visit the following week. Informed consent will be obtained by one of the investigators (Supplement, Figure F2).

#### Baseline visit

The baseline visit will take place between 4 to 6 weeks after hospital discharge. Information regarding the study will be given to the patient, and informed consent will be obtained. After that, the patient will be randomized. During this first visit, demographic data, medical history, and ICU and hospitalization variables will be collected from all the included patients, regardless of their randomization arm. All patients will complete a series of questionnaires to evaluate their quality of life and the presence of anxiety, depression, or post-traumatic stress disorder. The presence of pain and its influence on the patients’ lifes will also be evaluated.

Intervention group

The intervention consists of a program that includes early patient care, therapeutic education, and psychological intervention. It will be implemented across three medical visits scheduled as follows:
Visit 1 Intervention group, 4 to 6 weeks after hospital discharge.Visit 2 Intervention group, 8 weeks after hospital discharge.Visit 3 Intervention group, 18 weeks after hospital discharge.

Components:
Interview and physical examination.Therapeutic education about the PICS, orally and in writing with specific documents delivered at the end of the visit, i.e., a PICS fact-sheet developed by the investigators and a rehabilitation manual recommended by the Follow-up and Rehabilitation Committee of the Argentine Society of Intensive Care, SATI [14].Therapeutic education about pain (if the patient reports pain) which includes an explanation of pain neurophysiology, the rational use of drugs prescribed by other specialists, information about how to manage daily life activities, and the importance of pre-emptive pain management for proper rehabilitation.

A psychological intervention will be conducted if the following criterium is met: a score higher than 8 on the hospital anxiety and depression (HAD) test depression subscale (supplement, questionnaire Q1) [17]. The intervention protocol will consist of 7 weekly sessions lasting one and a half hours each (supplement, Table 1). The intervention in depression is based on Rehm’s model of self-control. Psychological interventions may cause adverse events resulting in worsening of patients’ clinical course (overdose, self-harm, and self-harm attempts). Therefore, the investigators will monitor any related symptom, report it as an adverse event, and refer the patient for treatment by a specialist unit.

#### Control group

Standard-of-care is as follows: patient follow-up will be carried out by their referring physicians (primary care physicians or specialists), who will not be involved in the study. After the baseline visit, the second and third visits will be phone call visits at 3 and 6 months after hospital discharge.

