**Methods:**

The PAINCOVID trial is a unicentric randomized, controlled, patient-blinded superiority trial with two parallel groups. The primary endpoint is the health-related quality of life at 6 months after hospital discharge, and randomization will be performed with a 1:1 allocation ratio. This paper details the methodology and statistical analysis plan of the trial and was submitted before outcome data were available.

The estimated sample size is 84 patients, 42 for each arm. Assuming a lost to follow-up rate of 20%, a sample size of 102 patients is necessary (51 for each arm).

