### Methods of randomization and bias minimization

Once the informed consent has been obtained, the patient will be assigned 1:1 by the investigator to either the control or intervention group according to the allocation sequence generated by the randomization program. Only the researchers who signed the informed consent had access to this list which was concealed from the principal investigator.

The data for the screening will be obtained from the clinical records program of the Hospital Clínic de Barcelona, where the data of patients who required admission to the ICU, as well as days of admission, will be reviewed by the members of the research team in order to verify whether they are eligible or not.

Screening for patients will be done monthly. Enrolment is expected to be completed within 3 to 6 months. The baseline visit will take place between 4 to 6 weeks after hospital discharge. Follow-up visits will take place at 3 and 6 months after discharge (Fig. 2.)

Patients will be encouraged to remain in the study during each interview by giving them feedback about the importance of their collaboration. Participants who decide to drop out during follow-up will be asked about the reason for it, and all their answers will be recorded.

The database will be paper-based and electronic data entry will also be used using FileMaker. Only three research team members will obtain access to this program. case report forms (CRF) will be kept in the hospital files and all data will be available on the web after study finalization.

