#### Outcome measurements

Demographic data will be collected at baseline visit, including age, gender, body mass index, smoking habits, socioeconomic level, work status, and marital status. Barthel index and medical history will also be recorded, especially psychiatric disorders, chronic pain, opioid usage, and previous ICU admission (Supplement, Table 2).

Data regarding ICU and hospital admission will be also collected: Acute Physiology and Chronic Health disease Classification System (APACHE II) and Sequential Organ Failure Assessment Score (SOFA) severity scores, days under invasive or non-invasive mechanical ventilation, presence of sepsis [18] (Supplement Definition, D5), need for tracheostomy, use of vasoactive drugs, acute kidney injury (Supplement Definition, D6) and need for renal replacement therapy, stress hyperglycaemia and hypoglycaemia (Supplement Definition, D6, D7), corticoid use, use of neuromuscular blocking agents, days under sedation, ICU acquired weakness, delirium presence, maximum value of ferritin, d-dimer and C reactive protein, and ICU and hospital length of stay. The Mini-Mental State Exam (MMSE) test, which is a widely used test of cognitive function among the elderly that assesses orientation, attention, memory, language, and visual-spatial skills, will be evaluated before answering the questionnaires [19].

The impact of the intervention program on health-related quality of life reported by the patient will be assessed through the European quality of life 5 dimensions/5 levels (supplement, questionnaire Q2) [20]. The questionnaire assesses the quality of life of study participants according to 5 domains: mobility, self-care, usual activities, pain/discomfort, and anxiety/depression, each scored according to a scale of 1 (no problems) to 5 (extreme problems) and generating a 5-digit code corresponding to the quality of life. The visual analog scale of the same test will also be assessed (from 0—worst imaginable health—to 100—best imaginable health). The questionnaire provides a simple descriptive profile of a respondent’s health status. Quality of life will be assessed at Baseline Visit and at 3 and 6 months after discharge.

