## Discussion

As far as we know, this is the first randomized clinical trial that examines the effectiveness of an early care therapeutic education and psychological intervention for the management of post-intensive care syndrome and chronic pain after COVID-19.

Patients who survive a critical illness often experience disturbances in many areas, with pain being one of the most important topics. Unfortunately, lack of adequate care to manage this pain is often a problem during the patients stay in the units [5]. This study would quantify the impairment on quality life after ICU admission, as well as the incidence of chronic pain, anxiety, depression, and PTSD. The health status derived from our analysis could be used in economic evaluations of healthcare systems and long-term impact and consequences of the pandemic. Likewise, if the effectiveness of our intervention is verified, it would serve as proof of the need to implement early care programs that allow the recovery process to be followed from early stages, given the current scenario of the pandemic.

Being an integral part of this syndrome, and in order to avoid the limitations and effects of pain on the patient’s quality of life, pain management should be introduced in the ICU.

This project has some limitations.

The main one is that patients meeting inclusion criteria (especially those who have had a more severe course of the disease) may have a severe mobility limitations that would prevent them from attending some trial visits, which would result in a selection bias. This would add to the problem of a small population sample as a consequence of the study being carried out in a single center.

In addition, there are risk factors associated with the development of PICS and chronic pain after a critical illness. These include older age, low socioeconomic status, female gender, previous mental health problems, negative ICU experiences, and delirium.

Therefore, an exploratory analysis of risk factors potentially associated with PICS due to COVID-19 will be carried out, although the sample size will be a determining factor in the conclusions

Future development of multi-center projects may overcome this limitation.

Finally, since this intervention program involves face-to-face visits, the pandemic could limit its correct development.

Restrictions on mobility might make hospital follow-up visits difficult.

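### The trial is labelled patient-blinded although patients can see which care they receive, and the mode of the 3- and 6-month assessments is fixed (telephone) for the control arm only

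*Protocol article*

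**What the plan says.** **Blinding.** The Methods part of the abstract calls the study a "randomized, controlled, patient-blinded superiority trial with two parallel groups". The Blinding section of the main text says single-blind without naming the blinded party. It then separates three staff roles: the investigator who administers the questionnaires, the pain physician and psychologist who deliver the intervention, and the analysts. It does not say that the questionnaire investigator is kept unaware of allocation.

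**What patients receive.** Under Baseline visit, patients are informed, consent and are then randomized. The intervention arm has three medical visits, oral and written education, and seven weekly psychology sessions for those above a depression-score threshold. Under Control group, patients are followed by their own physicians. No sham or attention control is described.

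**When and how outcomes are taken.** Outcome measurements states: "Quality of life will be assessed at Baseline Visit and at 3 and 6 months after discharge". The randomization section adds "Follow-up visits will take place at 3 and 6 months after discharge", with no mode. A mode appears only under Control group: "After the baseline visit, the second and third visits will be phone call visits at 3 and 6 months after hospital discharge". The programme visits after baseline are set elsewhere: "Visit 2 Intervention group, 8 weeks after hospital discharge" and "Visit 3 Intervention group, 18 weeks after hospital discharge". The Discussion notes that "since this intervention program involves face-to-face visits, the pandemic could limit its correct development", and then that mobility restrictions could hamper follow-up visits at the hospital.

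**The concern.** The primary outcome is health-related quality of life reported by the patient. For such an outcome, knowing one's treatment can change the answer without any change in health. A label of patient-blinded tells readers that this route to bias is closed. Nothing in the described design closes it.

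The second part concerns how the answers are collected. Randomization protects the comparison only if outcomes are measured alike in both arms. If controls answer by telephone and intervention patients answer face to face, any effect of mode on self-rating is added in full to the estimated treatment effect. The planned two-group tests cannot separate the two. Booking a call or a visit would also tell the questionnaire investigator the arm, even though that person takes no part in treatment.

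**Working it through.** **1. Can patients be blinded?** Three parts of the article bear on this.

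- Abstract: patients are blinded.
- Baseline visit and Control group: after consent, one arm attends education visits, receives written material and may attend psychology sessions. The other arm gets none of these and no substitute.
- Blinding: only staff roles are separated.

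The second item rules out the first, and the third does not supply it. This conclusion does not depend on the telephone question.

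**2. Does assessment mode differ by arm?**

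| | Control | Intervention |
|---|---|---|
| Programme visits after baseline | none | 8 and 18 weeks, face to face |
| Outcome assessments after baseline | 3 and 6 months | 3 and 6 months |
| Mode of those outcome assessments | telephone | not stated |

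Three and six months are about 13 and 26 weeks (52/4 and 52/2). The programme visits at 8 and 18 weeks therefore do not fall at the outcome times, and their being face to face does not show how outcomes are collected. The closest hint is the Discussion's remark on follow-up visits at the hospital. Controls are telephoned at follow-up, so the remark most naturally concerns the intervention arm, but it may mean programme visits. A difference in mode is plausible and permitted by the text. It is not stated.

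**3. Is the questionnaire investigator masked?** This is neither stated nor denied. If only controls are telephoned, mode reveals the arm. If both arms are telephoned, that argument falls away, although patients could still disclose their allocation.

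**4. Illustration of what a shift would do.** The document gives no figure for a mode or expectation effect and no SD.

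Inputs from Sample size: control mean 50 VAS points, difference 20%, one-tailed alpha 0.05, power 80%, 42 per arm. The 42 cannot be reproduced without an SD, so I solve for the SD that it implies:

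SD = δ × √(n/2) / (z_α + z_β)

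- Reading 20% as 10 points (20% of 50), one-sided: 10 × √21 / (1.645 + 0.842) = 18.4.
- The same with a two-sided test, as Data analysis specifies: 10 × √21 / (1.960 + 0.842) = 16.4.
- Reading 20% as 20 points on the scale doubles these to 36.9 and 32.7.

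With no true effect and an assumed shift b between arms, SE = SD × √(2/42), and the two-sided rejection rate is Φ(b/SE − 1.96) + Φ(−b/SE − 1.96).

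| Implied SD | SE | b = 2 | b = 3 | b = 5 |
|---|---|---|---|---|
| 18.4 | 4.02 | 7.9% | 11.6% | 23.7% |
| 16.4 | 3.57 | 8.7% | 13.4% | 28.8% |
| 36.9 | 8.04 | 5.7% | 6.6% | 9.5% |
| 32.7 | 7.14 | 5.9% | 7.1% | 10.8% |

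Example for SD 18.4 and b = 5: 5/4.02 = 1.243, and Φ(−0.717) + Φ(−3.203) = 0.2367 + 0.0007 = 0.237. Five points is half of a 10-point target difference. The table shows sensitivity to a shift, not evidence that there is one.

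**The case against.** The strongest reply is that the problem is one of labelling and brevity. The article condenses a fuller protocol, and its schedule figure is not shown here. Intervention patients may also be telephoned at 3 and 6 months, in which case mode is balanced. Most of this stands, and it limits what can be claimed:

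- A reader might infer that arm is confounded with assessment mode. The documents do not establish that: the face-to-face visits are programme visits at other times, and the intervention arm's outcome mode is not given.
- A reader might infer that the assessor is unblinded. That follows only if the modes differ. The separation of staff roles also stays true whatever the assessor knows.
- A reader might add that the cognitive screen, whose "visual-spatial skills, will be evaluated before answering the questionnaires", cannot be done alike by telephone. The article ties that screen to no follow-up visit, so it may be baseline only and carries no weight here.
- The false-positive rates rest on an assumed shift and a back-solved SD. They cannot be quoted as properties of this trial.

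The reply does not rescue the blinding label, which the article itself states and its own design contradicts. Nor does brevity fully explain the mode. The article specifies it for one arm, under that arm's own heading, and a reader cannot tell whether the other arm is treated alike.

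**Conclusion.** The point holds in two parts of unequal strength.

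**Established:** patient-blinded is wrong. Patients know whether they attend the programme, there is no sham, and the Blinding section supports only role separation. This matters because the primary outcome is self-reported, whether the VAS or the five-domain profile is analysed.

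**Conditional:** the 3- and 6-month assessment mode is given for controls only. If intervention patients are assessed in person, mode differs by arm on the primary outcome and reveals allocation to the questionnaire investigator. If both arms are telephoned, this part is closed by one sentence.

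The size of any bias is unknown. Under assumed shifts of 2, 3 or 5 VAS points and an SD near 18, the error rate would be about 8%, 12% or 24%. It would be lower if 20% means 20 points. No sample-size figure changes.

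**What to change.** 1. Replace patient-blinded with a statement that participants and therapists are not blinded. State the limit that this places on a self-reported primary outcome.
2. Collect the 3- and 6-month questionnaires in both arms by one common mode and script, separately from programme visits. Telephone is already set up for controls.
3. Keep the questionnaire investigator without access to allocation, and ask patients not to reveal it. Claim assessor blinding only if this is done.
4. If follow-up has already been collected, do not change mode retrospectively. Report the mode used in each arm and state the limitation. This may well apply: Trial status anticipated study completion by March 2021 and the article appeared in July 2021.

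**Cost:** amended wording and, if intervention patients were to be seen in person, two telephone calls each in place of in-person questionnaires. A little of the richness of in-person assessment may be lost.

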#### Outcome measurements

Demographic data will be collected at baseline visit, including age, gender, body mass index, smoking habits, socioeconomic level, work status, and marital status. Barthel index and medical history will also be recorded, especially psychiatric disorders, chronic pain, opioid usage, and previous ICU admission (Supplement, Table 2).

Data regarding ICU and hospital admission will be also collected: Acute Physiology and Chronic Health disease Classification System (APACHE II) and Sequential Organ Failure Assessment Score (SOFA) severity scores, days under invasive or non-invasive mechanical ventilation, presence of sepsis [18] (Supplement Definition, D5), need for tracheostomy, use of vasoactive drugs, acute kidney injury (Supplement Definition, D6) and need for renal replacement therapy, stress hyperglycaemia and hypoglycaemia (Supplement Definition, D6, D7), corticoid use, use of neuromuscular blocking agents, days under sedation, ICU acquired weakness, delirium presence, maximum value of ferritin, d-dimer and C reactive protein, and ICU and hospital length of stay. The Mini-Mental State Exam (MMSE) test, which is a widely used test of cognitive function among the elderly that assesses orientation, attention, memory, language, and visual-spatial skills, will be evaluated before answering the questionnaires [19].

The impact of the intervention program on health-related quality of life reported by the patient will be assessed through the European quality of life 5 dimensions/5 levels (supplement, questionnaire Q2) [20]. The questionnaire assesses the quality of life of study participants according to 5 domains: mobility, self-care, usual activities, pain/discomfort, and anxiety/depression, each scored according to a scale of 1 (no problems) to 5 (extreme problems) and generating a 5-digit code corresponding to the quality of life. The visual analog scale of the same test will also be assessed (from 0—worst imaginable health—to 100—best imaginable health). The questionnaire provides a simple descriptive profile of a respondent’s health status. Quality of life will be assessed at Baseline Visit and at 3 and 6 months after discharge.

Pain (presence and intensity) will be assessed by the Brief Pain Inventory (BPI) questionnaire (supplement, questionnaire Q3) [21] at the baseline visit and at 3 and 6 months after discharge. This questionnaire is a multidimensional questionnaire that evaluates pain intensity in the last 24 hours (worst, lowest, average) and current (right now). It also assesses the impact of pain on daily activities (general activity, encouragement, work, social interaction, sleep, enjoyment of life and the ability to walk). The questions are rated on a scale from 0 to 10, with 10 being the worst possible value. Subsequently, the average intensity score (BPI intensity score) and average interference score (BPI interference score) is calculated. Following IMMPACT recommendations, a clinically significant pain will be recorded if the mean intensity score (BPI intensity score) is greater than or equal to 3 [22].

If BPI is positive for pain, pain catastrophizing will be assessed by the Pain Catastrophizing Scale (PCS) (supplement, questionnaire Q4) [23] and patients will also complete the *Douleur Neuropathique en 4 Questions* (DN4) (supplement, questionnaire Q5) to screen for neuropathic pain [24]. The PCS consists of 13 questions that explore the frequency of thoughts and feelings that the interviewees have in the presence of current or anticipated pain, which are grouped into three scoring subscales (magnification, rumination and defencelessness). Each question is rated on a 5-point scale (0: not at all; 4: all the time). The maximum total score is 52 points. A score greater or equal than 30 will be considered as a clinically relevant level of catastrophizing.

The impact of the intervention program on the incidence of anxiety or depression will be assessed by the Hospital Anxiety and Depression test (HAD) (supplement, questionnaire Q1) [17], consisting of 14 questions, with two subscales, one for anxiety and the other for depression, with seven items each and a maximum score of 21 for each subscale. The cut-off points are as follows: 0 to 7 imply the absence of clinically relevant anxiety and depression, 8 to 10 imply de presence of symptoms that require consideration, and 11 to 21 it report the presence of relevant symptoms, with a very probable diagnosis of anxiety or depression. According to Bjelland’s review, cut-off points equal or greater that 8 will be used as abnormal anxiety or depression’s values. This test will be performed at the baseline visit and at 3 and 6 months [25].

Finally, the incidence of post-traumatic stress disorder (PTSD) [26] will be evaluated with the post-traumatic stress disorder checklist questionnaire (PCL-5) [27]. It contains 20 questions that correspond to the DSM-V criteria. Participants will rate their symptoms on a scale of 0 (not at all), 1 (slightly), 2 (moderately), 3 (quite) to 4 (extremely), with a score ranging from 0 to 80. The overall severity of the symptoms can be assessed adding up the scores of each question (interval 0–80). The severity of each symptom can also be evaluated adding up the scores of the questions. DSM-5 symptom cluster severity scores can be obtained by adding up the scores for the items within a given cluster, i.e., cluster B (items 1–5), cluster C (items 6–7), cluster D (items 8–14), and cluster E (items 15–20). A provisional PTSD diagnosis can be made by treating each item rated 2 (“moderately”) or higher as a symptom endorsed, then following the DSM-5 diagnostic rule which requires at least: 1 B item (questions 1–5), 1 C item (questions 6–7), 2 D items (questions 8–14), and 2 E items (questions 15–20) (supplement, questionnaire Q6).

For this analysis, questionnaire licensing was obtained. The validated version in Spanish was used for each of them, except for PCL-5 which, being a new questionnaire, is not yet validated in Spanish, but it has the advantage of screening PTSD according to the DSM-V criteria. The questionnaires are shown in the supplement.

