### Secondary outcomes

The secondary objectives are to determine if the intervention is superior to standard-of-care, by evaluating:
The HRQoL at three months after hospital discharge.The incidence of chronic pain and the degree of functional limitation at 3 and 6 months after hospital discharge.The incidence of anxiety and depression at 3 and 6 months after hospital discharge.The incidence of post-traumatic stress syndrome at 3 and 6 months after hospital discharge.

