### Study population

Adult patients will be enrolled if they fulfil at least one of the following Inclusion criteria: (1) had SARS-CoV-2 infection, confirmed with a respiratory tract sample using PCR-based tests, (2) had an Acute Physiology And Chronic Health Evaluation (APACHE II) score over 14, (3) ICU stay over 10 days, (4) acquired weakness in ICU [14] (Supplement, Definition D1), (5) delirium during ICU [14] (Supplement Definition, D2), and 6) acceptance to participate in the study by signing the informed consent form.

The exclusion criteria are as follows: (1) patients with non-confirmed SARS-CoV-2 infection according to WHO guidance [15], (2) central ervous system degenerative diseases or terminal illness (Supplement, Definition D3), (3) terminal illness (Supplement, Definition D4) [16], (4) insufficient understanding of the Spanish language, (5) patients with whom it would be difficult to complete follow-up, and (6) not willing to sign the informed consent form.

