### Data analysis

Qualitative variables will be presented as proportions, while for quantitative variables, the mean (standard deviation) or median (interquartile range), after checking for normality using the Shapiro-Wilk test, will be used. To compare variables across groups, Student *t* tests or Mann-Whitney *U* tests for continuous data and chi-square tests or exact tests for categorical variables will be carried out. Before parametric hypothesis testing, equality of variances will be studied using the Levene’s test, and if assumptions are not met, contrasts will be performed with the Welch’s test. An intention-to-treat approach will be followed. Two-tailed *P* values will be presented and a significance level of 0.05 will be used.

For the secondary outcomes, adjustment with the Benjamini-Hochberg procedure will be carried out.

A sub-analysis of the effect of treatment on compliers will be performed for the main outcome. Compliers are defined as those subjects that effectively receive the treatment they are allocated to. For the present study, compliers will be defined as individuals that, having been randomized to the intervention, complete at least two out of three medical visits and at least five out of seven psychological interventions. For the statistical analysis, instrumental variable analysis will be carried out. A two-sided probability (*p*) value of less than 0.05 will be considered to indicate statistical significance. The statistical analysis was performed using R (https://www.rstudio.com/) statistical software.

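### The outcome named incidence of chronic pain is, under the only case rule given, a point prevalence of clinically significant pain; the incidence outcomes for anxiety, depression and PTSD share the labelling problem.

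*Protocol article*

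**What the plan says.** The Secondary outcomes section of the protocol article lists "The incidence of chronic pain and the degree of functional limitation at 3 and 6 months after hospital discharge", and the Abstract repeats the aim. Incidence is also the word used there for anxiety, depression and post-traumatic stress.

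Under Outcome measurements, "Pain (presence and intensity) will be assessed by the Brief Pain Inventory (BPI) questionnaire" at the baseline visit and at 3 and 6 months. The recall window is short: "This questionnaire is a multidimensional questionnaire that evaluates pain intensity in the last 24 hours", together with pain at the moment of asking. One threshold is given: "a clinically significant pain will be recorded if the mean intensity score (BPI intensity score) is greater than or equal to 3".

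The same section has the medical history recorded at baseline, "especially psychiatric disorders, chronic pain, opioid usage, and previous ICU admission". None of the exclusion criteria under Study population concerns earlier chronic pain or pain at baseline. For group comparisons the Data analysis section says that "chi-square tests or exact tests for categorical variables will be carried out". It mentions neither restriction to patients free of the condition nor adjustment for baseline status.

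**The concern.** Incidence of chronic pain makes two claims: that the pain has lasted, and that it is new. The stated case rule secures neither. Someone with a sore back on the day of the 6-month call can reach the threshold. So can someone who had chronic pain for years before intensive care.

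Chronic pain is in the trial's title, and the Discussion proposes that the derived health status be used in economic evaluations. A one-day prevalence published as an incidence would overstate how much new chronic pain follows critical COVID-19. The between-arm contrast would also be estimated with pre-existing and transient pain mixed in, although baseline data that could account for part of that variation are collected.

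**Working it through.** The plan has no figure of its own to reproduce here. Its sample size (84, or 102 after allowance for loss) is built on the EQ visual analog scale, and no rate is stated for pain.

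**1. Named outcome against measured outcome**

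| Needed for incidence of chronic pain | What the article supplies |
|---|---|
| Minimum duration or persistence | None; the score covers 24 hours and the present moment, at one visit |
| New onset | None; prior chronic pain is recorded but not used |
| Population at risk at the start | All randomized patients; no exclusion for prior or baseline pain |
| Rule turning BPI into chronic pain | None; mean intensity of 3 or more is labelled clinically significant pain |

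The supplement definitions cited in the article (D1 to D7) are cited for other conditions, none for chronic pain.

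**2. What the rule counts.** Let b be the fraction already in pain at baseline, w the proportion of them still at or above the threshold at follow-up, and n the proportion of the others who are cases then. The observed proportion is b·w + (1 − b)·n. The new-onset proportion is n. The two agree only if b = 0 or w = n, and nothing in the article ensures either. The article in fact expects baseline cases: pain education is given to patients who report pain, and psychological treatment is triggered by a baseline depression score (Baseline visit section).

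**3. Validity of the test.** Randomization gives b the same expectation in both arms. With no program effect, the expected proportions are equal, so the unadjusted test is not biased.

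**4. Possible dilution (all rates assumed).** Power is for a two-sided 0.05 pooled two-proportion test with n = 42 per arm, the plan's evaluable number:

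power = Φ{[d − 1.96·√(2·p̄(1 − p̄)/n)] / √[(p1(1 − p1) + p2(1 − p2))/n]}

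Example, 30% against 15%: p̄ = 0.225 and the standard errors are 0.0911 and 0.0896, so (0.15 − 0.1786)/0.0896 = −0.319 and power is 0.375.

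*Transient pain* at rate t among those without persistent pain, unaffected by the program: p = persistent + (1 − persistent)·t.

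| t | Control | Program | Risk ratio | Power |
|---|---|---|---|---|
| 0 | 30.0% | 15.0% | 2.00 | 0.375 |
| 5% | 33.5% | 19.25% | 1.74 | 0.31 |
| 15% | 40.5% | 27.75% | 1.46 | 0.23 |
| 20% | 44.0% | 32.0% | 1.375 | 0.20 |

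*Prior pain* in a fraction f, counted as cases in both arms whatever the program does, with new pain 40% against 20%: p = f + (1 − f)·new.

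| f | Control | Program | Difference | Power |
|---|---|---|---|---|
| 0 | 40% | 20% | 20 points | 0.52 |
| 0.1 | 46% | 28% | 18 points | 0.40 |
| 0.3 | 58% | 44% | 14 points | 0.25 |

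The second table is an extreme case, because it gives the program no effect on existing pain.

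**5. What restriction to baseline-free patients would do.** Psychological treatment requires a depression score higher than 8 on the Hospital Anxiety and Depression (HAD) test; a depression case is 8 or more. Every patient who qualifies at baseline is therefore a baseline case, and a restricted depression analysis would drop all of them. For pain, if only 25 per arm were free of it at baseline (assumed), power at 30% against 15% would be 0.24, about the same as the 0.23 under 15% transient pain.

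**The case against.** The strongest reply is that the article never equates a BPI mean of 3 or more with chronic pain. Its own label for that score is clinically significant pain. Nor does it say that prior cases will be counted as incident. History of chronic pain and a baseline BPI are both collected, and the BPI is repeated, so onset and persistence could be derived. This stands as far as it goes: the fault is an unbridged gap between outcome and measurement, not a declared wrong definition. But the article gives case rules for pain, anxiety, depression and PTSD, says that it details the analysis plan, and offers no other route from BPI to chronic pain.

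A reader might go further and infer that the comparison is biased, or that pre-existing pain is dead weight which the program cannot influence. The documents support neither. Randomization balances prior pain in expectation. General procedures describes the program as covering both prevention and management, and pain education goes to patients who already report pain, so their later pain status is a legitimate treatment effect.

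A reader might also take the illustrated loss of power as the trial's own. None of the rates comes from the documents, and in the 30% against 15% scenario power is low even with no transient pain.

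**Conclusion.** The point holds as a matter of definition and precision. By the stated rule, the trial would report the prevalence of clinically significant pain at a visit under the name incidence of chronic pain. The outcomes for anxiety, depression and PTSD are prevalences in the same sense, because patients who are cases at baseline remain in the count.

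The between-arm test stays valid and the primary outcome, quality of life at 6 months, is untouched. The unadjusted comparison leaves unused the baseline information that could sharpen it. The direction of any dilution is clear where transient or unresponsive pain is present, but its size depends on rates the article does not give.

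The conclusion assumes that no definition of chronic pain in a part of the protocol not shown links the BPI result to duration and onset.

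**What to change.** - **Labels.** In the Abstract and Secondary outcomes, call single-visit proportions the prevalence of clinically significant pain, and the prevalence of anxiety, depression and PTSD, at 3 and 6 months.
- **Chronic pain.** Define chronic (persistent) pain at 6 months as BPI intensity of 3 or more at both the 3- and 6-month visits.
- **Main comparison.** Keep all randomized patients, adjusted for baseline status of the condition and, for pain, for history of chronic pain, for example by logistic regression. The Baseline visit section mentions randomization before the questionnaires, so confirm that they are completed before the first program contact if they are to serve as baseline covariates.
- **New-onset cases.** Report these among patients free of the condition at baseline only as a descriptive supplement, because the program also treats existing cases.

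The cost is some wording, one derived variable and baseline covariates, all from data already collected. The two-visit definition yields fewer cases and needs both visits observed, in a trial that assumes 20% loss, so the handling of a missed visit should be stated. Two 24-hour windows some three months apart also do not prove continuous pain, which is why persistent is the safer word.
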